#### **5.2.4. Adverse events**

##### **5.2.4.1. Adverse event definition**

The following definitions will be employed for the reporting of Adverse Events:

A) Adverse Event:

An adverse event is defined as any unfavourable and unintended sign, symptom, syndrome, or illness that develops or worsens during the period of observation in the clinical study. Clinically relevant abnormal results of diagnostic procedures including abnormal laboratory findings (e.g., requiring unscheduled diagnostic procedures or treatment measures, or resulting in withdrawal from the study) which are considered by the Principal Investigator to be detrimental should be recorded as adverse events whether or not they have a causal relationship with the study drug. Where the laboratory result is a sign of another clinical condition, the clinical condition itself should be the reported adverse event. An event unequivocally caused by a significant deterioration of the underlying condition related to malaria is regarded as an adverse event.

Occurrence of *P.falciparum* infection occurring during the course of the study will be captured on a specific form on the CRF. However these events will not be reported as adverse events unless the resulting malaria is of an unexpected severity.

B) Unexpected Adverse Event:

Any adverse experience that has not been previously observed (i.e. included in the protocol or Investigator's Brochure) whether or not the event is anticipated because of the pharmacologic properties of the study drug.

C) Serious Adverse Event

Any adverse experience occurring at any dose that results in any of the following outcomes:

- **Death.**
- **Life threatening-** defined as an experience that places the patient or subject, in the view of the Investigator, at immediate risk of death from the reaction as it occurred. (Note: this does not include a reaction that, had it occurred in a more severe form, might have caused death).
- Requires inpatient **hospitalisation** or prolongation of existing hospitalisation.
- Results in a **congenital** anomaly or birth defect.
- Results in a **persistent or significant disability** or incapacity.
- **Important medical events** that may not result in death, be life-threatening or require hospitalisation may be considered as a serious adverse drug experience when, based upon appropriate medical judgement, they jeopardise the patient or subject and may require medical or surgical intervention to prevent one of the outcomes listed above (for example, an event may be defined as serious based on a deterioration in grade in Toxicity Tables).

"Persistent or significant disability or incapacity" means that there is a substantial disruption of a person's ability to carry out normal life functions.

Medical and scientific judgement should be exercised in deciding whether expedited reporting is appropriate in situations where none of the outcomes listed above occurred. Important medical events that may not be immediately life-threatening or result in death or hospitalisation but may jeopardise the patient's health or may require intervention to prevent one of the other outcomes listed in the definition above should also usually be considered serious.

The following will not be considered as Serious Averse Events: cases of hospitalisation for elective surgery, need to observe high risk patients to prevent serious events, and visiting the emergency room due to suffering from adverse events but discharged after treatment without hospitalisation.

D) Alert terms and other reasons for expedited reporting to Pharmacovigilance

No specific events are subject to reporting as alert terms in this study.

Pregnancy should be reported **promptly** for tracking purposes but does not constitute as such an adverse event. The pregnancy should be reported on the Pregnancy Report Form. The pregnant patient must be followed until birth of the child and the outcome of the pregnancy and birth reported to the Sponsor. However, any adverse outcome to the mother, foetus or newborn must be regarded as a serious adverse event and must be **immediately** reported to the Sponsor.

Worsening of the baseline conditions that are judged by the Investigator to be more significant than normal daily fluctuation of the disease symptoms should be regarded as adverse events.

Prior to randomisation, study site personnel will note the occurrence, nature and severity of each patient's medical condition(s). During the study, site personnel will note any change in the condition(s) and/or the occurrence and nature of any adverse events.

At each visit the patient will be asked about any change in his/her condition since the last evaluation.

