#### Fixed-dose combination of pyronaridine artesunate

The goal of anti-malarial drug development is to develop potent, safe, easy-to-administer and inexpensive combination therapies. Importantly, there is a need for new drugs that are efficacious against both *P. falciparum* and *P. vivax*, because in areas where both species exist and health systems are undersourced, it is often not possible to distinguish between the two species at the initial diagnosis. Given the data accumulated to date, it is anticipated that the combination of pyronaridine and artesunate, a new ACT, will fulfil these needs.

A large multicentre dose ranging study of fixed pyronaridine artesunate combination in acute uncomplicated malaria patients has been completed recently. The pyronaridine artesunate combination was shown to be highly effective and well tolerated in the dose range intended for the final product.

A single tablet strength containing 180:60 mg pyronaridine artesunate has been selected for development and licensing, to ease the administration, dosing regimen as well as the maintenance of inventory in low income countries.

Taken together, this forms the rationale for developing the fixed-dose combination pyronaridine artesunate (3:1) 3-day regimen for the treatment of blood stage *P. vivax* malaria, in parallel to its development in *P. falciparum* malaria.

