**5.2.4.3. Adverse event reporting requirements**

All adverse events must be recorded on the standard Adverse Events Form in the CRF. All serious adverse events occurring during the study must be recorded on the SAE Form. These reports are to be made whether or not the Investigator considers the serious adverse events to be related to the investigational drug.

A full written report to the Sponsor's Medical Monitor will include the SAE Form, photocopies of pertinent test results and medical notes / study records, consultant report(s), hospital discharge summary and autopsy report (if relevant and as soon as available to the Investigator), and a summary of the outcome of the reaction plus the Investigator's opinion of drug relationship to the serious adverse event(s). The provision of this report must not delay reporting of the SAE to the Sponsor as described below.

The Investigator or his / her staff will notify the Independent Ethics Committee (IEC) of all SAEs as soon as possible and in accordance with local regulations.

Adverse events and / or laboratory abnormalities identified in the protocol as critical to safety evaluations shall be reported by the Investigator to the Sponsor according to the reporting requirements and within the time periods specified for serious adverse events.

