#### Primary Efficacy Endpoint

The primary efficacy endpoint for the study is the cure rate on Day 14.

Cure on Day 14 will be defined as no parasitemia on Day 14 irrespective of axillary temperature without previously meeting any of the criteria of treatment failure throughout the follow-up period.

Treatment failure is defined as any of the following:

- ◆ Clinical deterioration due to *P. vivax* illness requiring hospitalization in presence of parasitemia.
- ◆ Presence of parasitemia and axillary temperature  $\geq 37.5^{\circ}\text{C}$  any time between Day 3 and Day 28.
- ◆ Presence of parasitemia on any day between Day 7 and Day 28 irrespective of clinical condition.

Patients presenting a *P. falciparum* infection after clearance of *P. vivax* parasites should be treated accordingly and withdrawn. They should not be considered as *P. vivax* treatment failures.

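### The adverse event exemption for in-study P. falciparum infection tests severity and not seriousness, so on a literal reading a hospitalised case need not be reported as an SAE

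*Protocol*

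**What the plan says.** Section 5.2.4.1 (A) opens with a broad definition of an adverse event: "any unfavourable and unintended sign, symptom, syndrome, or illness that develops or worsens during the period of observation in the clinical study". A new P. falciparum malaria falls within it. The last paragraph of (A) then takes it out. P. falciparum "infection occurring during the course of the study will be captured on a specific form on the CRF", but "these events will not be reported as adverse events unless the resulting malaria is of an unexpected severity".

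Section 5.2.4.1 (C) defines a serious adverse event as "Any adverse experience occurring at any dose that results in any of the following outcomes". One of those outcomes is inpatient admission "or prolongation of existing hospitalisation".

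Section 5.2.4.3 requires that "All serious adverse events occurring during the study must be recorded on the SAE Form", and section 5.2.4.4 adds the 24-hour telephone and form route.

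Section 9.5.1 (Primary Efficacy Endpoint) says that patients with P. falciparum infection after clearance of P. vivax "should be treated accordingly and withdrawn", and does not count them as P. vivax failures.

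**The concern.** The exemption depends on whether the severity was expected. SAE status depends on outcome. These are different properties, and 5.2.4.1 (A) lets the first decide whether the second is ever examined. An SAE is an adverse experience with a listed outcome. If the infection has been ruled not to be an adverse event, a site that follows (A) to the letter has no event to which the criteria in (C) could apply.

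Comparing safety is part of the primary objective (section 2), and medical monitors depend on prompt SAE reports. A reporting definition also has to be right in the protocol: an analysis plan can add a table later, but it cannot restore an expedited report that was never filed.

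**Working it through.** The protocol states no figure on this point, so there is none to reproduce. The check sets the provisions side by side.

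| Place in the protocol | Effect on a patient admitted with P. falciparum malaria of expected severity |
|---|---|
| 5.2.4.1 (A), general definition | Adverse event: an illness that developed during observation |
| 5.2.4.1 (A), P. falciparum exemption | Not reported as an adverse event |
| 5.2.4.1 (C), seriousness criteria | Serious, because admission is a listed outcome |
| 5.2.4.1 (C), list of admissions and visits that are not SAEs | Not on the list, so not exempted there |
| 5.2.4.2, note on severe versus serious | Reporting duty follows seriousness and not severity |
| 5.2.4.2 (C), Action Taken | Admission is also to be reported as an SAE |

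Four of these six lines point to SAE reporting or fail to exempt the case, the general definition makes it an adverse event, and one line removes it. Three further observations suggest that the gap is a drafting fault and not a deliberate choice.

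1. Section 5.2.4.1 (D) says that pregnancy is not in itself an adverse event, but then makes any adverse outcome for mother, foetus or newborn an SAE with immediate reporting. That exemption has a seriousness override. The P. falciparum exemption has none.
2. Section 5.2.4.1 (A) counts significant deterioration of the underlying malaria as an adverse event. An admission for worsening P. vivax malaria is therefore reportable, while an admission for a new P. falciparum malaria of expected severity is not.
3. Section 5.2.4.1 (B) defines an unexpected event by reference to the protocol or the Investigator's Brochure. It does not say what severity of P. falciparum malaria counts as expected, so sites have no common standard.

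The other routes were then checked as possible substitutes.

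- Action Taken (5.2.4.2) is a field completed for an adverse event. If none is opened, the field may not be reached.
- Alert terms (5.2.4.1 (D)): none are specified for this study.
- The CRF form, and the reason for discontinuation (3.3, with withdrawals as a safety criterion in 5.2), leave a record but carry no SAE timeline.
- The status report (5.2.4.5) is weekly. It names treatment failure, which P. falciparum cases are not, and otherwise clinically relevant findings.

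**Size, on assumptions that are not in the protocol.** The only documented input is 228 patients per arm (section 9.4). Assume a P. falciparum incidence of 1% to 10% over 42 days in an arm, with 5% to 20% of cases admitted.

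- Infections = 228 × incidence: 228 × 0.01 = 2.3, to 228 × 0.10 = 22.8.
- Admissions = infections × proportion admitted: 2.28 × 0.05 = 0.1, to 22.8 × 0.20 = 4.6.

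The range spans a factor of (10/1) × (20/5) = 40, all of it due to the assumptions.

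With equal arms and RR as the ratio of PA to chloroquine incidence, the chloroquine share of cases is 1/(1 + RR). It is 83% at RR 0.2, 67% at RR 0.5 and 50% at RR 1.0. The protocol supplies no RR.

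**The case against.** The strongest reply is that the protocol, read as a whole, already makes such a case an SAE. Admission is a listed outcome in 5.2.4.1 (C), Action Taken in 5.2.4.2 says to report it, P. falciparum is not among the stated non-SAE situations, and an investigator could reasonably treat any case needing admission as unexpectedly severe. This stands in part. It means that the protocol does not bar such reports, but it also means that two sites following it faithfully could act differently.

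Three stronger readings are tempting, and the documents support none of them.

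- A reader might infer that these events can never become SAEs, or are lost. The first is one reading of conflicting text. The second is wrong: the cases are recorded on the CRF form and as withdrawals, and possibly in the weekly report. What can be missing is the AE or SAE entry and the expedited report.
- A reader might infer that the omissions fall mainly in the chloroquine arm. The Introduction makes this plausible: it says that "there is a need for new drugs that are efficacious against both" P. falciparum and P. vivax, acknowledges chloroquine-resistant P. falciparum, and reports Phase II cure above 95% with PA. It gives no P. falciparum rate by site or arm. An imbalance in that direction would under-count comparator events and so would not favour PA.
- A reader might compare about one missed admission (228 × 0.05 × 0.10 = 1.1) with the 456 × 4/477 = 3.8 patients with an SAE expected at the Phase II rate, and conclude that some 30% of SAEs go missing. That divides an assumed one-arm count by a two-arm total. The rate also comes from patients treated for P. falciparum malaria, all on PA.

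It is also fair to say that tabulating the P. falciparum form can be left to the statistical analysis plan. Section 9.5.2 plans only frequencies and percentages for SAEs, so no formal test depends on this.

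**Conclusion.** The point holds as an internal contradiction in a stated reporting rule. The exemption in 5.2.4.1 (A) uses an undefined severity test with no exception for serious cases. Followed literally, it can keep a hospitalised P. falciparum case off the SAE Form and out of the 24-hour route, contrary to 5.2.4.1 (C) and 5.2.4.2. The consequence is possible incompleteness of the AE and SAE tables and of expedited reporting, for patients in either arm.

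Its size cannot be derived from the protocol. The illustrative 0.1 to 4.6 admissions per arm rests entirely on assumed incidence and admission rates and shows only that the number could be anything from negligible to a handful. No conclusion about direction between arms is warranted beyond the conditional one above. The primary efficacy analysis is not involved.

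**What to change.** Reconcile 5.2.4.1 (A) with 5.2.4.1 (C) and 5.2.4.2 by extending the exemption, after the severity condition, with: *or meets any seriousness criterion in (C), in which case it is reported as an SAE*. This mirrors the override already written for pregnancy. It would help to state in the same place what is meant by unexpected severity, so that sites apply the remaining exemption alike.

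The change affects reporting only and leaves treatment and withdrawal rules untouched. The cost is one clause in the protocol and a few more SAE forms.

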#### Choice of comparator

In spite of the increasing numbers of resistant strains, chloroquine monotherapy is still recommended as standard blood-stage therapy for patients with *P. vivax* malaria in the countries in which this trial will be conducted. Its selection as comparator is therefore justified. The adult dose of chloroquine will be 620 mg for 2 days followed by 310 mg on the third day and for children 10 mg/kg for the first two days and 5 mg/kg for the third day. Total dose is in accordance with the current practice in the countries where the study is conducted. The safety profile of chloroquine is well established and known. Although generally well tolerated, the following side-effects of chloroquine treatment have been described:

Gastro-intestinal disturbances, headache, hypotension, convulsions, visual disturbances, depigmentation or loss of hair, skin reactions (rashes, pruritus) and, rarely, bone-marrow suppression and hypersensitivity reactions such as urticaria and angioedema. Their occurrence during the present trial may however be unlikely given the short (3-day) duration of treatment.

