#### **Non-clinical Summary**

ICH-compliant pre-clinical studies have been conducted to GLP on pyronaridine, artesunate and the combination. The clinical study material has been produced to GMP standard by the Sponsor, Shin Poong Pharm, in conjunction with the Medicines for Malaria Venture (Pyronaridine Artesunate Investigator Brochure, Edition 3, March 2006).

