### ***Phase I Data with Pyronaridine-Artesunate Combination***

A randomised, blinded phase I clinical study has been conducted with the fixed ratio combination of pyronaridine artesunate (3:1). The protocol combined multiple objectives of single and multiple dose-rising phases as well as food-effect and drug-interaction sub-studies. Four dose levels of pyronaridine artesunate were investigated in the single and multiple rising dose parts (6:2; 9:3; 12:4; 15:5 mg/kg pyronaridine artesunate, respectively). The study recruited healthy male and female subjects aged 19-40 years: 9 per group (7 active 2 placebo) in the single-rising dose; 10 per group (5 male, 5 female) in both the interaction and food effect studies; 8 per group (6 active 2 placebo) in the multiple dose-rising part. Dose escalation was approved by medical reviewers and Investigators on review of safety data. Assessments consisted of safety evaluation (vital signs, ECG, lab tests, adverse events), up to 14 days after dosing. With single and multiple dosing (once daily for 3 days), no individual clinically significant sustained drug-related changes were recorded in vital signs, ECGs and clinical laboratory tests. The adverse events at doses studied were minor or moderate in nature and resolved without sequelae. No serious or severe adverse events were reported. The adverse event profile was consistent those reported in the literature for both components and are predominantly gastrointestinal in nature. No subject discontinued treatment due to adverse events including vomiting. In summary, the combination was well-tolerated up to and including the dose ratio of 15:5 mg/kg,

with only mild or moderate adverse events, including gastrointestinal effects, observed. No significant food effect was reported and there was no notable drug interaction effect.

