### **7.2.2. Sponsor responsibilities**

Sponsors' representatives will promptly notify all concerned Investigators, IEC and the regulatory authorities of findings that could adversely affect the safety of patients, impact the conduct of the study, or alter the IEC's approval/favourable opinion to continue the study. In addition, Sponsors' representatives will expedite the reporting to all concerned Investigators/institutions, to the IEC and to the regulatory authorities of all adverse drug reactions that are both **serious and unexpected**.

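### The definition of an unexpected adverse event has no product or severity test, so a literal reading narrows the sponsor's expedited-reporting rule

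*Protocol*

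**What the plan says.** Section 5.2.4.1 of the protocol sets the definitions to be used in reporting adverse events. Item (B) defines an unexpected event as "Any adverse experience that has not been previously observed (i.e. included in the protocol or Investigator's Brochure"), and adds that this holds "whether or not the event is anticipated because of the pharmacologic properties of the study drug". No other section of the protocol defines the term.

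Section 7.2.2 then uses the word. The sponsors' representatives are to expedite reporting to the investigators and institutions concerned, to the ethics committee and "to the regulatory authorities of all adverse drug reactions that are both serious and unexpected".

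Two parts of the Introduction determine what counts as included in the protocol:

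- Choice of comparator lists the effects of chloroquine, beginning with "Gastro-intestinal disturbances, headache, hypotension, convulsions, visual disturbances" and ending with "bone-marrow suppression and hypersensitivity reactions such as urticaria and angioedema".
- The summary of phase I data says that PA was well tolerated up to the highest dose studied, "with only mild or moderate adverse events, including gastrointestinal effects, observed".

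The only brochure the protocol names is the one for PA ("Pyronaridine Artesunate Investigator Brochure, Edition 3, March 2006", in the Non-clinical Summary).

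**The concern.** Expectedness is the filter that decides which serious reactions the sponsor must send out quickly. A sound filter asks whether this reaction, in this form, is already known for the product under suspicion. Item (B) asks only whether the experience already appears in one of two documents, and one of those documents also describes the comparator's side-effects.

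The reactions that say most about a new combination are those not seen with it before and those worse than seen before. These are the ones a literal reading can class as already observed. About 228 patients, children among them, are planned for the PA arm (section 9.4). Section 4.5 keeps all parties blind, so whoever judges expectedness will usually not know which drug was given and cannot repair the wording by looking at the arm.

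**Working it through.** No arithmetic applies. The check reads the definition together with the rule that uses it, and then with the other reporting routes.

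**Product.** Take a serious convulsion or marrow suppression in a patient on PA.
1. Is it included in the protocol? Yes, through the chloroquine list.
2. Is it then unexpected under 5.2.4.1(B)? On the literal wording, no.
3. Does it meet the serious-and-unexpected condition in 7.2.2? No.
4. Does the protocol's clinical summary of PA (phase I and phase II) name it as a PA effect? No.

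Gastrointestinal disturbance is also on the chloroquine list, but it is already recorded for PA in phase I and so is not newly masked. Headache and loss of pigment or hair are less likely to be serious. That leaves six groups: hypotension, convulsions, visual disturbances, skin reactions, marrow suppression and hypersensitivity.

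**Severity.** Take a life-threatening form of a gastrointestinal effect that the phase I summary records only as mild or moderate.
1. Has the experience been observed before? Yes, in kind.
2. Does the definition ask about degree? No. Section 5.2.4.1(A) refers to unexpected severity, but only for intercurrent *P. falciparum* malaria, so the idea does not carry over to (B).
3. Does the event meet 7.2.2? On the literal wording, no.

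**The clause on pharmacology.** The second half of (B) stops an event from becoming expected merely because pharmacology would predict it. That widens the definition slightly, but adds neither a product test nor a severity test.

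**Where such an event still goes.**

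| Route | Who is told | Expectedness filter? |
|---|---|---|
| 5.2.4.4 | Medical monitors, pharmacovigilance group, sponsors (site report within 24 hours; life-threatening or fatal events to the Central Medical Monitor within 2 hours) | None |
| 5.2.4.3 and 10.1 | Ethics committee, for serious events; 10.1 speaks of those from the study site | None |
| 7.2.1 | Authorities, if the medical monitor so decides | No criterion stated |
| 7.2.2, first sentence | Investigators, ethics committee, authorities, for findings that bear on safety | None, but no event-level trigger |
| 7.2.2, second sentence | Investigators, ethics committee, authorities | Serious and unexpected |

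The last row is the only event-level criterion the protocol states for expedited notice to other sites' investigators and ethics committees and to regulators. It depends on the word defined in (B). Section 5.2.4.3 also gives accelerated reporting to events the protocol identifies as critical, but 5.2.4.1(D) says that no specific events are alert terms.

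**The case against.** The strongest reply is that the safeguards are substantial and do not depend on expectedness. All serious events move inward within a day, the site's ethics committee hears of them, and a medical monitor reviews each one and decides on reporting to the authorities. This stands. A reader might infer that these events go unreported, or never reach regulators; the documents do not support that.

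Second, nothing in the text says that a listing for one drug counts for another, or that severity is to be ignored. Both are inferred from silence. The chloroquine effects appear under a heading about the comparator, and treating them as PA's known effects is not the most natural reading. Section 7.2.2 does not cite 5.2.4.1(B) either. This also stands, so the point concerns what the wording permits, not what the sponsor intends. Still, (B) is the protocol's only definition of the term, and a reporting rule should not depend on readers supplying the missing limits.

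Third, two relevant documents are not shown. The PA Brochure may already list some of these effects, or severer forms of them, and the Safety Monitoring Plan announced in 5.2.4.5 may set a better test. The phase I summary is also not the whole PA record: the phase II summary reports 6 serious events in 4 patients, 2 of them possibly or probably related, without naming them. So the claim that any particular effect is new for PA is conditional. The fault in the definition is not, because a separate plan should not have to override what the protocol says.

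A reader might also argue that everything named in the toxicity tables of Attachment 7 counts as included in the protocol. The wording does not exclude it, but a grading scale is plainly not a record of prior observation, and the point does not need it.

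**Conclusion.** The definition is badly fixed and should be changed. It has no severity test and no link to the suspected product, and read literally it lets two kinds of informative serious reaction fall outside the sponsor's stated expedited-reporting rule.

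The size is modest. The gap is confined to event-level notice to other sites' investigators and ethics committees and to regulators, where a discretionary decision and a general duty remain. The number of reports affected cannot be derived from the protocol and is probably small. Sample size and the efficacy analysis are untouched.

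The conclusion assumes that 7.2.2 uses the word as 5.2.4.1(B) defines it, and that the Safety Monitoring Plan does not replace that definition. Which effects are new for PA depends on the Brochure.

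**What to change.** 1. Reword 5.2.4.1(B): an event is unexpected if its nature or severity is not consistent with the reference safety information for the suspected product, meaning the Investigator's Brochure for PA and the product information for chloroquine and for primaquine.
2. Remove listing in the protocol as a criterion.
3. Refer to this definition in 7.2.2.
4. State in the protocol or the Safety Monitoring Plan how expectedness is judged while treatment is blinded. Judging the case as though PA had been given is one workable convention, but not the only one; what matters is that one is fixed.

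The cost is about a paragraph of text and possibly a few more expedited reports. It needs no new data, visits or patients.
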